#### 3.2.3. Eating Self-Regulation Markers

The reward value of food (i.e., implicit wanting/explicit liking and wanting) will be measured by a computer procedure, the Leeds Food Preference Questionnaire (LFPQ) [58,59], which uses a “forced choice” reaction time measure of implicit wanting in addition to explicit subjective measures of liking and wanting for visual food stimuli varying in fat content and taste. To measure implicit wanting, the question “Which food do you most want to eat right now?” will be presented and the participant will be required to choose between a pair of food images as quickly as possible (with minimum thinking). The speed with which one category of stimuli is chosen relative to alternative categories provides a quantifiable measure of implicit wanting for each food category in the procedure. Reaction times as well as frequency of choice will be recorded. Explicit liking and wanting measures will be obtained by rating the same stimuli according to a 100-mm visual analogue scale (VAS), with a total of 16 food images, after prompting the subjects with the statements ‘‘How pleasant would it be to experience a mouthful of this food now?’’ for explicit liking and ‘‘How much do you want some of this food now?’’ for explicit wanting. For both scales, the anchor “Not at all” will be used on the left side of the scale and “Extremely” on the right side. Both questions will be presented intermittently and in a random order. Finlayson et al. showed that this questionnaire is sensitive to changes in the physiological state induced by eating and exercise, which suggests that it is suitable for capturing the changes in food reward when a change in individual’s state occurs [58,60]. It has been previously used in individuals with overweight and obesity, as well as in anti-obesity drug trials [61,62].

Intuitive eating and motivations to regulate eating will be assessed using internationally validated questionnaires, namely the Intuitive Eating Scale—2 (IES-2) [63] and the Regulation of Eating Behavior Scale (REBS) [64]. IES-2 is a 23-item questionnaire that measures the degree to which one eats in response to physiological eating cues, comprising 4 subscales: eating for physical rather than emotional reasons (Cronbach’s α = 0.92), unconditional permission to eat (Cronbach’s α = 0.81), reliance on hunger and satiety cues (Cronbach’s α = 0.85), and body-food choice congruence (Cronbach’s α = 0.83) [63]. Participants respond to the stem “For each item, please check the answer that best characterizes your eating attitudes or behaviors” on a 5-point Likert scale ranging from 1 (“strongly disagree”) to 5 (“strongly agree”). REBS comprises a total of 24 items, organized into 6 subscales, measuring amotivation, external, introjected, identified, integrated, and intrinsic motivations. Following the stem “Why are you regulating your eating behaviors?”, participants respond on a 7-point Likert scale ranging from 1 (“does not correspond at all”) to 7 (“corresponds exactly”). Prior research has supported REBS’s factor structure and reliability (Cronbach’s alphas >0.70) [64].

#### 3.2.4. Blood Samples

Measurement of glucose, lipid profile, including total cholesterol, low (LDL) and high-density lipoprotein (HDL), cortisol and hepatic enzymes will be performed in serum samples using colored enzymatic tests, in an automated analyzer (Cobas Integra 400). Insulin assessment will be performed in an automated analyzer (Cobas Integra 400) by eletroquimioluminescence. HbA1c will assessed by high-performance liquid chromatography. High sensitive C-reactive protein will be determined by nephelometry. Homeostatic model assessment for insulin resistance (HOMA-IR), a procedure to quantify insulin resistance, will be calculated through the following equation [65,66]:$$HOMA-IR=\;\frac{Fasting\;Insulin\;\left(\mu U/mL\right)\;\times \;Fasting\;Glycemia\;\left(mmol/L\right)\;}{22.5}$$

Reference values for cholesterol and its components [67], *Glycemia* [68] and thyroid panel [69] will be considered.

Metabolic syndrome (MetSyn) may be present whenever at least 3 of the 5 following risk factors are present in a participant: (a) abdominal obesity, characterized by an abdominal circumference higher than 102 and 88 cm for men and women, respectively; (b) hypertriglyceridemia, that is values of triglycerides equal or higher than 150 mg/dL; (c) low HDL cholesterol, identified by values of HDL cholesterol equal or below 40 or 50 mg/dL for men or women, respectively; (d) high arterial blood pressure, when systolic and diastolic arterial blood pressure are equal or higher than 135 and 85 mmHg, respectively; (e) hyperglycaemia, that is fasted glucose equal or higher than 100 mg/dL [70].

Blood derived-indices will also include the assessment of the thyroid panel (T3, T4, TSH) by immunoassay with chemiluminescent detection (Millipore Corp., Billerica, MA, USA,) and leptin levels by ELISA (enzyme-Linked Immunosorbent Assay).

### 3.3. Physical Fitness

#### 3.3.1. Cardiorespiratory Fitness Test

Maximal cardiorespiratory capacity will be assessed using the Bruce protocol test [71] performed on a variable speed and incline treadmill (Quinton Treadmill, Model 640, 90 TM Series). Simultaneously, the ventilated gas volumes, flow rates, and respiratory gas exchange will be determined by an open-circuit spirometry system (MedGraphics Corporation, Breezeex Software). Maximal oxygen uptake (VO_2_max) will be achieved when the two following criteria are obtained: a respiratory exchange ratio equal or greater than 1.10 for females and males aged to 20–49 y and equal or greater than 1.05 for females and males aged to 50–64 y [72], and no increase in VO_2_max despite further grade increases. The assessment will be performed at baseline and at 12 months.

#### 3.3.2. Strength Tests

The handgrip strength test evaluates the maximal isometric force of the muscles of the hand and forearm and will be assessed by a portable hand dynamometer JAMAR plus digital (Sammons Preston, Bolingbrook, IL, USA). Participants will be assessed on both hands alternately, in a standing position. Prior to the test, the grip dynamometer will be adjusted to the size of the hand of each subject. Handgrip assessment will be conducted with the subject standing up with the arms in a neutral position (halfway between supine and pronation position). Each participant will be assessed on both hands alternately until reaching three attempts for each hand. In each attempt, the subject will exert the maximal grip strength on the handgrip dynamometer with the assessed hand for 5 s. After each attempt, there will be a resting period of 60 s that will be used both for recovery and for changing the handgrip dynamometer to the opposite hand. The assessment is performed at baseline and at 12 months.

For the lower body strength, we will use the maximum strength of the leg by performing a horizontal leg press isometric test (S0409, BPH) with the bent leg and the knee joint at an angle of 110°. Participants will complete 5 maximal voluntary repetitions lasting 30 s, and a period of rest between reps of 60 s. All participants will be asked to produce strength the fastest they possibly can in all repetitions. The Plux software (Biosignalsplux) will be considered to analyze the highest value between the maximal voluntary repetitions. All participants will be instructed not to perform a Valsalva manoeuvre during the tests. The assessment will be performed at baseline and at 12 months.

#### 3.3.3. Resting Systolic and Diastolic Blood Pressure

Three measurements of systolic and diastolic blood pressure will be obtained with the participant in the sitting position using a digital sphygmomanometer. The blood pressure cuff-fixed on the nondominant upper arm is loosened during the two min pause between the measurements. The arithmetic means of the second and third readings are considered as the participants’ blood pressure and pulse values, respectively. Overall, there is a rest of approximately five minutes before the second blood pressure measurement is carried out. The cut-off values of 140 mmHg for systolic blood pressure and 90 mmHg for diastolic blood pressure will be considered [73].

#### 3.3.4. Exercise Motivation

The Behavioral Regulation in Exercise Questionnaire—3 (BREQ-3) [74,75] will be used to assess motivations to engage in exercise. BREQ-3 contains 24 items, organized into 6 subscales, measuring external, introjected (i.e controlled motivational regulations), identified, integrated, and intrinsic motivations (i.e, autonomous motivational regulations). Following the item “why do you exercise”, participants respond on a 5-point Likert scale ranging from 0 (“not true for me”) to 4 (“very true for me”). Prior research has supported BREQ’s factor structure and reliability (Cronbach’s alphas >0.70) [74,75,76].

#### 3.3.5. Quality of Life

To measure general health-related quality of life, participants will complete the Short-Form Health Survey (SF-36) questionnaire [77], with a total of 36 items composed of eight dimensions: physical functioning (Cronbach’s α = 0.83), physical role limitations (Cronbach’s α = 0.89), bodily pain (Cronbach’s α = 0.88), general health (Cronbach’s α = 0.82), emotional role limitations (Cronbach’s α = 0.74), social functioning (Cronbach’s α = 0.71), vitality (Cronbach’s α = 0.86), and mental health (Cronbach’s α = 0.90) [77]. These dimension scores will be summarized into two composite scales, a physical component summary and a psychological/mental component summary. Statements such as ‘‘During the past 4 weeks, I cut down the amount of time I spent on work or other activities’’ will be answered with yes or no; questions such as ‘‘How much bodily pain have you had during the past 4 weeks?’’ will be evaluated on a 6-point Likert scale from none to very severe. Higher scores indicate better health-related quality of life.

#### 3.3.6. Statistics

Statistical analysis will be performed using IBM SPSS statistics version 24.0 (IBM, Chicago, IL, USA). To test the normality of distribution of the variables, the Kolmogorov–Smirnov test will be performed. Descriptive statistics will be calculated (mean, standard deviation, and range). If normality is not achieved in some variables, non-parametric methods will be used. Repeated measures with Bonferroni corrections for adjusted comparisons will be used to determine any differences between conditions at the three moments and for changes between the intervention and control groups over time in primary and secondary outcomes. For exploring the association between changes in body composition and metabolic parameters, linear mixed regression models will be conducted. Statistical significance will be set at *p* < 0.05.

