#### 3.3.7. Sample Size

For sample and power calculations, this study is powered on changes in total body fat assessed by DXA. We consider a type I error of 5% and a power of 80% (using the software GPower version 3.1.9.2) to detect an effect size of 0.58 for statistically significant differences in total body fat as reported elsewhere [78]. A total of 37 participants per group will be required. Considering a 20% drop out rate, as occurred in the selected study [78], we will enroll 94 participants (47 in each group).

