In addition, prior research has shown an increase in upper and lower body strength after diet and exercise programs [84]. Other studies have shown that after lifestyle interventions, an increase of cardiorespiratory fitness occurs [84,85,86]. Therefore, it is expected that after the Champ4life intervention, participants reveal an increase in physical fitness, leading to higher muscle quality, better cardiorespiratory fitness, and lower mortality [86].

We also expect to understand the metabolic and behavioral compensations that may occur during weight loss and maintenance. We aim to find any compensations which lead to the retake of initial weight, like changes in energy intake and expenditure [20], spontaneous PA [21], and adaptive thermogenesis [22]. The current literature shows that when we increase EE (by increasing PA), we may compensate by increasing sedentary behavior, decreasing lifestyle PA and/or increasing energy consumption during the rest of the day [87]. The mechanisms underlying adaptive thermogenesis (i.e, mainly the decrease in REE and PAEE), beyond what can be predicted from the changes in FM and FFM in response to a restricted EI [19], are unclear when modest weight loss is expected. The mechanisms underlying the interplay between PA and alterations in eating behaviors and dietary intake (in terms of quantity and quality) also require further exploration, in order to improve interventions’ efficacy.

A significant strength of the Champ4life program will be the SDT-based intervention, providing tools for the adoption and sustainability of healthy behaviors through the development of autonomous motivation and self-regulatory skills [30,32,83]. Some limitations are anticipated in this study and should be addressed, in particular the effect of confounding variables such as the large age range (18–65 years) of participants eligible to be included, retirement years, and an unbalanced gender representation, provided there are more male former athletes than females.

To address these issues, the analysis will be controlled for the potential effects of these confounders. In addition, the prevalence of eating disorders is higher among athletes, especially in those engaged in weight-sensitive sports [88,89], and this may also be the case with former athletes; still, this aspect might not be appropriately captured by initial screening procedures (relying on yes/no answers) and thus will constitute a limitation of the present study.

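### A normality pre-test on the raw variables decides, outcome by outcome, whether the planned group-by-time comparison and covariate control can be carried out

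*Protocol article*

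**What the plan says.** Section 3.3.6 (Statistics) sets a two-step rule. First: "To test the normality of distribution of the variables, the Kolmogorov–Smirnov test will be performed". Then: "If normality is not achieved in some variables, non-parametric methods will be used". No test is named for the second step, and no outcome is exempt.

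The same section plans repeated-measures analyses at the three assessments, including "for changes between the intervention and control groups over time in primary and secondary outcomes".

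The Discussion (Section 4) names three possible confounders: "the large age range (18–65 years) of participants eligible to be included, retirement years, and an unbalanced gender representation". It continues: "To address these issues, the analysis will be controlled for the potential effects of these confounders". It also expects more men than women.

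The article does not say how this control, or the comparison of change between groups, is kept for a variable that fails the test.

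**The concern.** Three features of the rule are at issue.

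- **Target.** A repeated-measures or covariate-adjusted model needs roughly normal residuals. It does not need normal raw variables. A body-composition variable pooled over men and women is a mixture of two distributions, and can fail although the residuals given sex are normal.
- **Conflict.** Mann–Whitney, Wilcoxon and Friedman tests, in their usual forms, take no covariates and have no group-by-time term. A variable sent to them loses what Section 3.3.6 and the Discussion each promise, unless a less usual rank method is chosen.
- **Data-driven choice.** Whether an outcome is reported as a mean difference or a rank comparison, and with or without adjustment, depends on a test run on the trial's own data, separately for each variable.

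At stake is whether the outcomes share one pre-specified estimand. If the fallback compared raw follow-up values, much of the power would be at stake too.

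**Working it through.** **Inputs from the article (Section 3.3.7).** Effect size 0.58, type I error 5%, power 80%, 37 evaluable per group, 20% dropout, 94 enrolled.

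**Inputs assumed, because the article gives none.** 65% men; normal distributions within sex; the sex gaps, log-SDs and baseline-to-follow-up correlations r shown below; the Kolmogorov–Smirnov test with estimated mean and SD (Lilliefors form) at 5%.

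**1. The plan's own figures.**
- Enrolment: 37 / (1 − 0.20) = 46.25, rounded up to 47 per group, 94 in total. This reproduces.
- One-sided: n = 2(1.645 + 0.842)² / 0.58² = 36.8, so 37. This reproduces.
- Two-sided: 2(1.960 + 0.842)² / 0.58² = 46.7, so 47. Two-sided power at 37 per group is 0.69–0.70.

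Sidedness is a separate matter. It is shown here only because it explains why the two-sided powers in step 5 start near 0.70 rather than 0.80.

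**2. How often the test rejects when nothing is wrong.** With truly normal data and 47 per group, simulation gives about 5% for one pooled variable, 12% for at least one of three time points, and 23% for at least one of six group-by-time cells. Independent tests would give 1 − 0.95³ = 14% and 1 − 0.95⁶ = 26%; the correlation between time points lowers these a little. The article does not say which of these sets is tested.

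**3. How often the test rejects for other shapes (n = 94).** Ranges are over repeated simulations.

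| Shape assumed | Rejection |
|---|---|
| Sex gap 1.5 SD or less | about 5–6% |
| Sex gap 2 SD | 12–14% |
| Sex gap 2.5 SD (% fat 28 vs 38, SD 4) | 34–37% |
| Sex gap 3 SD (% fat 28 vs 40, SD 4) | 70–71% |
| Log-normal, log-SD 0.25 | 37–42% |
| Log-normal, log-SD 0.30 | 54–55% |
| Log-normal, log-SD 0.40 | 78–80% |

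With the 2-SD gap, at least one of the three pooled time points fails in 29% of samples. The residuals of the baseline- and sex-adjusted model fail in 4%. Those switches have no cause in the model.

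**4. Total fat mass in kg.** Take assumed fat-free masses of 68 kg (men) and 48 kg (women) with the % fat values above.
- Men: 68 × 0.28 / 0.72 = 26.4 kg.
- Women: 48 × 0.38 / 0.62 = 29.4 kg, or 48 × 0.40 / 0.60 = 32.0 kg.
- Gap: 3.0 to 5.6 kg. At a within-sex SD of 5–8 kg this is 3.0/8 = 0.4 SD to 5.6/5 = 1.1 SD.

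That lies below 1.5 SD. Simulation of this mixture gives 3–5% rejection, the nominal rate.

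**5. Power if a switch occurs (two-sided, 37 per group).** The effect is 0.58 SD of the change score. With unit SD at each time, the SD of change is √(2(1 − r)), so the effective standardised difference is:
- change score: 0.58;
- raw follow-up value: 0.58 × √(2(1 − r));
- baseline-adjusted model: 0.58 × √(2/(1 + r)).

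At r = 0.7 these are 0.58, 0.45 and 0.63. Simulated power:

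| Analysis | r = 0.5 | r = 0.7 | r = 0.9 |
|---|---|---|---|
| Baseline-adjusted linear model | 0.80 | 0.75 | 0.72 |
| t test on change | 0.68 | 0.68 | 0.70 |
| Mann–Whitney on change | 0.65 | 0.66 | 0.68 |
| Mann–Whitney on raw follow-up | 0.66 | 0.45 | 0.18 |

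A repeat run gave 0.46 for the raw follow-up comparison at r = 0.7. Mann–Whitney on change loses 2–3 points against the t test on change. Only the raw follow-up comparison loses much, and only when r is high.

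**The case against.** The strongest reply is that the article says only that non-parametric methods will be used. It does not say that covariates or the group-by-time comparison are dropped, or that baseline is ignored. Naming the fallback can be left to an analysis plan not shown, and rank methods that keep adjustment or compare changes do exist. This stands: a reader might infer that the plan discards them, but that is an inference from the usual forms of these tests.

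The reply also limits the harm to the primary outcome.
- A reader might infer that pooling the sexes makes total fat likely to fail. Step 4 shows that this need not happen for fat mass in kg. The high mixture rates concern % fat and fat-free mass. Abdominal fat was not examined.
- A reader might set the raw follow-up rank test against the baseline-adjusted model and report that gap as the cost. Section 3.3.6 plans a comparison of changes and does not promise baseline adjustment, so the like-for-like cost is 2–3 points.
- A reader might infer that a failed test leaves no estimate of effect size. Section 3.3.6 calculates means and SDs regardless of the test, and rank methods can report a location shift.

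Two more points stand. For skewed markers the residuals of an untransformed model are non-normal too (78% fail at an assumed log-SD of 0.6), so there the trigger is not spurious; the weakness is the unnamed fallback. And the uncorrected Kolmogorov–Smirnov test rejects far less often (0.2–7% at gaps of 2–3 SD), while the article does not say which form is meant.

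None of this removes the stated rule. It tests the wrong quantity, covers the primary outcomes, and is not reconciled with the adjustment and the comparison over time that the article promises.

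**Conclusion.** The concern holds as a defect in a stated rule, not as proof that the primary analysis will fail. Section 3.3.6 lets a test on raw variables decide the method and estimand of each outcome, and the usual replacements carry neither the promised covariate control nor the group-by-time comparison.

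A switch is most likely for markers that are commonly skewed, such as insulin, HOMA-IR, triglycerides, C-reactive protein and leptin, and for variables with a large sex gap, such as % fat or fat-free mass. For total fat mass in kg no excess over 5% is shown. The power cost is small if changes are ranked and large only if raw follow-up values are compared.

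The rates rest on assumed sex gaps, log-SDs, correlations and share of men, and on the Lilliefors form of the test. The conflict between the passages rests on none of these.

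**What to change.** Delete the normality pre-test and the switch. In their place:

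- use one mixed model for every continuous outcome, with group, time and group-by-time, adjusted for baseline, sex, age and years since retirement;
- pre-specify log transformation for insulin, HOMA-IR, triglycerides, C-reactive protein and leptin;
- inspect model residuals instead of raw distributions;
- give a bootstrap or robust-standard-error interval as a sensitivity analysis.

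This brings Section 3.3.6 into line with the Discussion. Section 3.3.6 already uses linear mixed models for the association analyses, so the method is not new to the plan.

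The cost is wording in the analysis plan, with no extra data or participants. The one drawback is that log-scale outcomes are reported as ratios rather than differences in original units. The change should be made while the outcome data are still blinded, as Section 2.4 provides until data entry is complete.

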We are also expecting to find barriers in the recruitment process due to the inclusion criteria. Despite the adherence promotion efforts, we may have some difficulties in retaining the participants throughout the study, due to its duration (~1 year), in particular those randomized to the control group. To minimize this risk, the control group is, in fact, a waiting list comparison group that is offered the program after the 12-month follow-up.

In conclusion, we anticipate that Champ4Life will be a novel and unique approach to improve athletes’ healthy lifestyle in post-career life. This project will provide evidence on the effectiveness of the Champ4Life program delivered to former athletes and will offer insight on the impact of changing PA, sedentary behavior, and diet on body composition and secondary outcomes, such as EB regulation and overall health-related markers. The findings from this project will enable evidence-based decisions for the implementation of lifestyle interventions for post-career transition.

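### The repeated-measures method named for the primary outcomes, if it is classical ANOVA, would drop anyone with a missed visit and could bias the fat-mass comparison; a mixed model on all randomised participants is the safer choice

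*Protocol article*

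**What the plan says.** Section 3.3.6 (Statistics) gives one method for the main comparison: "Repeated measures with Bonferroni corrections for adjusted comparisons will be used to determine any differences between conditions at the three moments". The same sentence applies this method to how the two arms differ in their course, for every primary and secondary outcome. The software is fixed: "Statistical analysis will be performed using IBM SPSS statistics version 24.0". The next analysis sentence gives mixed models a different job: "For exploring the association between changes in body composition and metabolic parameters, linear mixed regression models will be conducted".

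On drop-out, Section 3.3.7 (Sample Size) says: "Considering a 20% drop out rate, as occurred in the selected study [78], we will enroll 94 participants". The allowance is the same for both groups, since 37 becomes 47 in each. Section 4 (Discussions) says separately that keeping participants for about a year may be difficult, "in particular those randomized to the control group". It gives no rate per arm.

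The article also describes countermeasures. Section 2.7.1 stresses attendance at assessments however well a participant is doing, with the stated aim of avoiding differential attrition. Section 4 presents the waiting-list offer as a way to reduce the risk among controls.

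Body composition, including DXA, is measured at baseline, 4 months and 12 months (Abstract, Table 1).

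**The concern.** Section 3.3.6 shows that the authors have mixed models available and assign them to a secondary question. The contrast suggests that the primary method is the classical repeated-measures ANOVA (in SPSS, the GLM repeated-measures procedure). That procedure needs a complete row per person. Someone scanned at baseline and 4 months but lost before 12 months contributes nothing, although a primary outcome has been measured after randomisation.

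The comparison then runs between those who completed all visits, not between the groups as randomised. This is harmless in some circumstances. It is not harmless when the people who leave differ in outcome from those who stay and the pattern differs between arms. The article raises both ingredients itself: Section 4 foresees harder retention among controls, and Section 2.7.1 is concerned with attrition linked to success in the programme. Its only answers are retention efforts and the waiting-list offer. If these fall short, the named analysis gives no protection. At stake is the estimated effect on total and abdominal fat, the trial's primary aim.

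**Working it through.** **1. The plan's own figure.** Inputs from Section 3.3.7: effect size 0.58, type I error 5%, power 80%, drop-out 20%.

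- Normal approximation, n per group = 2(z_alpha + z_beta)² / d². One-sided 5%: 2(1.645 + 0.842)² / 0.58² = 36.8, so 37. This reproduces the stated 37.
- Inflation: 37 / (1 - 0.20) = 46.25, so 47 per group and 94 in total. This reproduces too.
- A two-sided 5% test would need 46.7, so 47 evaluable per group. Sidedness is not stated; that is a separate matter.

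**2. Does losing incomplete cases break the sample size?** With 20% lost in each arm, 47 × 0.8 = 37.6, about 38 per arm, and one-sided power is 0.81. With 10% lost from intervention and 30% from control, 47 × 0.9 = 42.3 and 47 × 0.7 = 32.9, so 42 against 33, and power is 0.80. Both match the plan's 80%, so the question is bias and not numbers.

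**3. Bias in the completer contrast.** The documents give no drop-out mechanism, so all of these inputs are assumptions:

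- changes in SD units, SD 1; true group difference -0.58 at both 4 and 12 months;
- correlation between the 4- and 12-month changes 0.7 (0.6 in brackets);
- logistic drop-out after month 4, with log-odds rising by 1 per SD worse 4-month change (odds × 2.7) where outcome-related;
- very large simulated samples, so the differences shown are bias and not sampling error.

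The completer estimate is the difference in mean 12-month change among those who remain. The all-data estimate regresses the 12-month on the 4-month change within arm and averages over everyone, as a likelihood-based model would under missing at random.

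| Drop-out, intervention / control | Related to outcome? | Completers | All data |
|---|---|---|---|
| 20% / 20% | no | -0.58 (-0.58) | -0.58 |
| 10% / 30% | no | -0.58 (-0.58) | -0.58 |
| 20% / 20% | yes, same in both arms | -0.58 (-0.58) | -0.58 |
| 15% / 25% | yes, same direction | -0.52 (-0.53) | -0.58 |
| 10% / 30% | yes, same direction | -0.47 (-0.48) | -0.58 |
| 20% / 20% | yes, intervention arm only | -0.70 (-0.68) | -0.58 |

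Relative to 0.58, the 10%/30% case is (0.58 - 0.47)/0.58 = 19% too small. The last case is (0.70 - 0.58)/0.58 = 21% too large. At correlation 0.6, halving the drop-out slope to 0.5 per SD moves the 10%/30% result from -0.48 to -0.52.

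**4. Limit of the remedy.** If drop-out at 10%/30% depends on the unseen 12-month value (correlation 0.6), completers give -0.42 and the all-data estimate -0.47. Both are biased, the second less so.

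**The case against.** The strongest reply is that the article never says incomplete cases are dropped. It names no ANOVA or GLM procedure, no complete-case set and no listwise deletion. SPSS can also fit a repeated-measures model with Bonferroni-adjusted comparisons as a mixed model. Analysis sets and missing-data rules are commonly left to a full protocol or SAP that is not shown, and their absence from an article is no fault. All of this stands: listwise deletion is an inference. It remains the natural inference because the same section reserves mixed models for another question.

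A reader might also infer that the plan expects its 20% loss to fall mainly on controls. The documents do not support this. The 20% in Section 3.3.7 comes from a cited study and is applied equally; Section 4 says only that there may be difficulty, more so among controls, without a rate. Under equal loss with a common mechanism the completer contrast is unbiased.

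The illustration is sensitive to its assumptions, and the all-data estimate stays at -0.58 partly by construction: drop-out was made to depend on a 4-month value that everyone has. Participants lost before month 4 have no such value to use. So the mixed model improves on the completer analysis but does not guarantee an unbiased result.

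**Conclusion.** The point holds in a limited form. Read as classical repeated-measures ANOVA, the named primary method would exclude participants with a missed visit and discard post-randomisation DXA data, in a trial whose authors foresee harder retention among controls. The completer contrast can then err in either direction, so it cannot be defended as conservative. In the assumed scenarios tabulated above, a true -0.58 SD appears as anything from about -0.47 to -0.70.

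That size depends on drop-out being related to outcome and differing between arms in rate or mechanism. Without either condition there is no bias. It would go too far to conclude that the plan prescribes a completer analysis, that it predicts drop-out concentrated in controls, or that the trial loses its planned numbers: the first is an inference, the second joins two separate statements, and the 20% allowance already covers the third.

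This should be fixed; confidence is medium.

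**What to change.** Replace the unspecific wording in Section 3.3.6 for the primary outcomes with a linear mixed model (SPSS MIXED) on all randomised participants, in the groups to which they were randomised, using every available moment. Adjust for baseline, for sex (the stratification factor in Section 2.4), and for the age and retirement-years covariates that Section 4 already promises. Name the group difference at 12 months as the target.

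Keep the completer analysis as a sensitivity analysis. Add a second one that lets drop-out depend on unobserved values, for example by shifting the assumed outcomes of drop-outs by arm over a stated range, because the mixed model reduces that bias without removing it.

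If a mixed model was meant all along, saying so settles the main point. The cost is a few sentences of analysis text and some syntax in the software already chosen. No extra visits, measurements or participants are needed.
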